### Laboratory evaluations

*Blood samples*: Blood samples will be taken by venipuncture into EDTA and serum tubes and kept at 2–8°C in cool boxes. Within four hours of collection the samples will be processed by the MRCG@LSHTM laboratory. EDTA samples will be run on an automated haematology analyser (Sysmex XN 1500) to measure haemoglobin concentration, to obtain a full blood count and to assess reticulocytes. Serum samples will be centrifuged and aliquots will be stored at -80°C. Samples will be analysed using a biochemistry analyser (Cobas Integra 400 plus) for iron markers (ferritin, transferrin, transferrin saturation, unbound iron-binding capacity, soluble transferrin receptor, and inflammatory markers [c-reactive protein/alpha-1 acid glycoprotein]). One of the serum aliquots will also be used to measure hepcidin, erythroferrone and erythropoiein concentrations using commercially available ELISAs.

*Faecal samples*: At baseline and endline a faecal sample will be collected, and iron content measured. Gut pathogens including bacteria, protozoa, intestinal helminths and viruses will be detected using real-time polymerase chain reaction multiplex assays. 

### Outcomes

*Primary:* Serum iron concentration on Day 99, after 98 days of iron supplementation and a one day wash-out period. Serum iron will be measured in venous blood collected at trial enrolment and 98 days after initiation of iron supplementation.

The primary endpoint is serum iron concentration at Day 99.

Secondary endpoints relating to iron status (all at Day 99) are:

a) Haemoglobin concentration.b) Percentage of infants with anaemia (defined as: haemoglobin < 110 g/L).c) Percentage of infants with iron deficiency anaemia (defined as: haemoglobin < 110 g/L, soluble transferrin receptor /logferritin ratio < 2.0, and ferritin < 12 ug/L or < 30 ug/L in the presence of inflammation).d) Hepcidin concentration. e) Reticulocyte number. f) Erythropoietin concentration.g) Erythroferrone concentration.

The secondary objectives are to test whether iron supplementation at this age is safe.

Endpoints related to this objective are:

a) Maternal reports of illness.b) Adverse events.c) Serious adverse events.d) Changes in gut pathogens and microbiota during the study period.e) Markers of environmental enteric dysfunction (EED).

The study will also assess potential impacts on growth, breastfeeding and feacal iron losses:

Endpoints related to these objectives are:

a) Anthropometric Z-scores relative to the World Health Organization (WHO) Growth Reference.b) Duration of exclusive breastfeeding.c) Faecal haemoglobin and iron. 

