Lastly, we will explore to what extent the magnitude of the intervention effect on serum iron concentration depends on iron status at baseline, as indicated by plasma concentrations of ferritin and soluble transferrin receptor (with adjustment for plasma concentrations of c-reactive protein/alpha-1 acid glycoprotein at baseline as inflammation markers).

**
*Mixed methods study.*
** The focus group discussions and in-depth interviews will be recorded and later transcribed and translated (where needed) into English. Translation will occur at MRCG@LSHTM by a trained employee literate in both Mandinka and English.

Data will be analysed with respect to the implementation framework known as
*Acceptability of healthcare interventions: an overview of reviews and development of a theoretical framework* (
Figure 4)
^
20
^.

The qualitative data will be uploaded into, managed, and analysed in NVivo (2020 release) using a Template Analysis Method
^
21,
22
^. The template will be based on the six themes in the acceptability framework, with some minor variation to make analytical sense with regards to our data. By this we mean the framework itself is a macro-level conceptual framework and will require semantic changes to some terminology for it to be useful to analyse at the meso-level (i.e., data from focus group discussions with stakeholders) and at the micro-level (i.e., data from in-depth interviews with women enrolled in the trial). Template analysis follows a methodical six-stage process: 1) Data re-familiarization; 2) Preliminary coding; 3) Thematic organization within the template; 4) Defining the template; 5) Application of template to the full dataset; and 6) Finalization of template definitions. By utilising the acceptability framework as the basis for the analytical template in both the focus group discussions and in-depth interviews datasets-, the qualitative data will be able to be linked coherently across all levels. An analysis in this detail should provide valuable insight about the acceptability of the intervention. We acknowledge that the domains may not all reach saturation, but as these are based on an extensive search of the literature by the framework authors, and have been tested in different fields, we propose to use these as a basis for our analysis. We will later analyse the extent to which the framework was valuable in this evaluation study. 

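### The iron deficiency anaemia endpoint has its sTfR/log-ferritin inequality reversed, so the most iron-depleted infants are the ones it fails to count

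*Protocol article*

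**What the plan says.** The protocol article, under Outcomes, introduces a list with "Secondary endpoints relating to iron status (all at Day 99) are". The third item is "Percentage of infants with iron deficiency anaemia (defined as: haemoglobin < 110 g/L", followed by two further conditions: "soluble transferrin receptor /logferritin ratio < 2.0, and ferritin < 12 ug/L or < 30 ug/L in the presence of inflammation". The three conditions are joined by 'and', so an infant must meet all of them to be a case.

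The definition appears nowhere else in the article, so no other section corrects or explains the direction of the ratio condition. The Statistical analysis section uses the same two markers as measures of baseline iron status ("as indicated by plasma concentrations of ferritin and soluble transferrin receptor") but gives no cut-off there. Laboratory evaluations lists ferritin, sTfR, C-reactive protein and alpha-1 acid glycoprotein among the assays.

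**The concern.** A composite case definition should have its parts select in the same direction. Here the ferritin condition selects infants with little stored iron. The ratio condition, as printed, keeps infants whose ratio is low. Because ferritin enters through the denominator, a low ratio goes with higher ferritin, and the two conditions work against each other.

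Two consequences follow if the rule is applied literally. First, infants with the clearest depletion are left out of the case count. Second, the comparison between arms can be misdirected. Supplementation that lifts an anaemic infant's ferritin from very low to just under 12 ug/L can turn that infant from a non-case into a case, while a more depleted infant on placebo stays uncounted.

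This is a named secondary endpoint on iron status in a trial whose purpose is to show that iron supplementation improves iron status.

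**Working it through.** **Inputs.** From Outcomes: haemoglobin < 110 g/L; ratio < 2.0; ferritin < 12 ug/L, or < 30 ug/L with inflammation. The article gives neither the sTfR unit nor the log base. I take mg/L and log10, and repeat the limits with natural log. The article states no expected rate or power for this endpoint, so there is no planned figure to reproduce.

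**Step 1: direction.** Let R = sTfR / log(ferritin). For ferritin above 1 ug/L, log(ferritin) is positive and increasing, so R rises as ferritin falls at fixed sTfR. This is true in any log base and any sTfR unit.

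**Step 2: what R < 2.0 requires.** For ferritin above 1 ug/L, R < 2.0 is the same as sTfR < 2 × log(ferritin). The largest sTfR that still passes is:

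| Ferritin (ug/L) | 2 × log10 | 2 × ln |
|---|---|---|
| 30 (limit with inflammation) | 2.95 | 6.80 |
| 12 | 2.16 | 4.97 |
| 6 | 1.56 | 3.58 |
| 4 | 1.20 | 2.77 |
| 2 | 0.60 | 1.39 |

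The permitted sTfR shrinks as ferritin falls.

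**Step 3: fixed-sTfR examples (log10).** At sTfR 2, with ferritin below 12 throughout:

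- ferritin 11.9: R = 1.86, counted
- ferritin 8: R = 2.21, not counted
- ferritin 5: R = 2.86, not counted
- ferritin 3: R = 4.19, not counted

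At sTfR 3, ferritin 40 gives 3/log10(40) = 1.87 and ferritin 10 gives 3/log10(10) = 3.0. The infant with ample ferritin meets the ratio condition (though not the ferritin condition), and the depleted infant fails it. With natural log the switch point moves but the pattern does not. At sTfR 4, ferritin 11.9 gives 4/2.48 = 1.62 (counted) and ferritin 5 gives 4/1.61 = 2.49 (not counted).

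**Step 4: effect on the comparison.** Take two anaemic infants with sTfR 2 (log10), one at ferritin 11 and one at ferritin 5. Their ratios are 2/log10(11) = 1.92 and 2/log10(5) = 2.86. Only the better-supplied infant is a case.

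**Step 5: illustrative size.** A simulation with assumed distributions used a median ferritin of 15 ug/L, log-normal markers, a shared depletion factor that lowers ferritin and raises sTfR, log10, and ferritin floored at 1.05 ug/L inside the ratio. That sTfR rises in deficiency is general physiology and is not stated in the article. Haemoglobin and inflammation were not modelled. Among infants with ferritin < 12 ug/L, the share meeting the ratio condition was:

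| Assumed median sTfR (mg/L) | < 2.0: all | < 2.0: least depleted quarter | < 2.0: most depleted quarter | > 2.0: all | > 2.0: least depleted quarter | > 2.0: most depleted quarter |
|---|---|---|---|---|---|---|
| 1.5 | 46% | 84% | 9% | 54% | 16% | 92% |
| 2 | 17% | 44% | 1% | 83% | 56% | 99% |
| 3 | 1% | 3% | 0% | 99% | 97% | 100% |

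At medians of 4 and 5 the printed rule counts essentially nobody.

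**Step 6: edge of the scale.** At ferritin of exactly 1 ug/L the log is zero and the ratio is undefined. Below 1 ug/L the ratio is negative, so the infant passes < 2.0 automatically. This does not rescue the rule, and it matters for the correction too.

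**The case against.** The strongest reply accepts the contradiction and disputes its weight.

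- **Size.** The extent of the undercount depends on sTfR levels, unit and log base, none of which the article gives. The ceiling at ferritin 12 more than doubles between log10 and natural log (2.16 against 4.97), and the simulated share counted runs from 46% to nearly nothing. This stands: a near-empty endpoint is one end of a range, and a skewed subset is the other.
- **Examples.** The ferritin 40 example shows only how the ratio condition behaves, since that infant fails the ferritin limit and is never a case. With natural log, ferritin 10 at sTfR 3 gives 3/2.30 = 1.30 and passes. Both points are fair, but neither changes the direction.
- **A slip, and recoverable.** This is probably a one-character error in one of seven secondary iron-status endpoints of a pilot. The raw markers are measured, so infants can be reclassified without losing data. That limits the cost of repair. It does not make the published definition usable, and a later silent change would be an undocumented change to a named endpoint.
- **The repair.** Nothing in the article shows that 2.0 is the right cut-off for this assay and log base. With > 2.0, an infant with ferritin below 1 ug/L would be wrongly excluded. This stands and is dealt with in the fix.

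The missing unit and log base may sit in the full protocol or analysis plan, and their absence is not counted as a fault. The direction of the inequality is different, because the article states it and states it wrongly.

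**Conclusion.** The point holds. As printed, the definition requires low ferritin and also a condition that excludes infants as ferritin falls, so it misclassifies in a known direction: the most depleted infants are lost first. That conclusion needs only the article's own formula and ferritin above 1 ug/L.

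The size is not fixed by the documents. Under the assumed distributions with log10 and mg/L, the printed rule keeps between 46% of low-ferritin infants (median sTfR 1.5) and 1% or fewer (median 3 or more). At medians 1.5 and 2 it keeps 9% and 1% of the most depleted quarter. The net direction of the bias between arms cannot be stated in advance, because iron would also move infants out of the anaemia and low-ferritin conditions.

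The fault is confined to this secondary endpoint. Serum iron, the sample size, and the separate haemoglobin and anaemia endpoints are untouched. It should be corrected before the endpoint is analysed.

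**What to change.** Choose one of two changes to the endpoint definition.

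1. Reverse the ratio condition to > 2.0, state the sTfR unit and log base beside it, and have the investigators confirm that 2.0 suits that assay and base. Add a rule for ferritin at or below 1 ug/L, for example that such infants are taken to meet the ratio condition, so that an undefined or negative ratio does not exclude them.
2. Drop the ratio and define the endpoint as haemoglobin < 110 g/L plus ferritin < 12 ug/L, or < 30 ug/L with inflammation. This is simpler and avoids the unit, base and edge-of-scale questions, but it is a different endpoint and should be recorded as such.

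Make the change before the Day 99 iron markers are classified, and record it as a dated correction. Study status puts the last follow-up in March 2022, after the article was written. If classification has already been done, report which rule was used and give the result under the corrected one.

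The cost is one line of text. Every marker needed is already in the laboratory plan, and no new data or samples are required.

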### Mixed methods study of parent and stakeholder attitudes

The mixed methods approach will explore the effects of the clinical intervention on relevant outcomes while observing and gathering information on implementation. We will use qualitative and quantitative methods to explore the acceptability of the intervention proposed in the main study. Given that the main study is an efficacy trial, it is not possible to assess the full implementation and scale up of such a trial to the real-world setting. Instead, the proposed research will explore the acceptability of iron supplementation in young infants.

**
*Consent for mixed methods study.*
** Prior to conducting focus group discussions and in-depth interviews, topic guides and interview schedules will be piloted among the study team. One investigator and a second female interviewer will pilot the focus group topic guides on members of the study team and adjustments will be made from the feedback. For practice, mock in-depth interviews will then be conducted by the female interviewer on the study team members. Not only will this help adjust the focus group topic guides and in-depth interviews schedules, but likewise, this will act as an opportunity for the interviewers to familiarise themselves with the questions and structure of the focus group discussions and in-depth interviews.

All potential participants for the qualitative data collection will be given written information in English in the form of a participant information leaflet and given adequate time to read it before agreeing to take part. Illiterate participants will have the information leaflet read to them by a trained member of the research team in their preferred language who will also sign to confirm their participation in consent. A copy of the signed informed consent form will be given to the participants.

### Data collection, management, and processing

Type of data: Four types of data, quantitative (demographic questionnaire and anthropometric) and qualitative (focus group discussions and in-depth interviews), will be collected.

**
*Quantitative.*
** Data collected from questionnaires on demography, daily review of 24-hour recall of health/morbidity from parents/guardians and weekly feeding questionnaires.

Anthropometric measurements, vital signs, adverse events, and stool questionnaire.

The clinical intervention from which we will gain the quantitative materials will be from the pilot study. We will use data collected from health questionnaires and from study endpoints. This data will be collected on site and stored via a secure data capturing platform (REDCap). This data will be collected by the field workers and will be fully anonymised. The data used for quantitative analysis will include:

Baseline demographic dataLaboratory data Adherence ratesDaily health data (adverse events and serious adverse events)Weekly infant feeding data

For the quantitative data, no patient-identifiable data will be included. The consent and data collection for this component will fall under the remit of the pilot study.

**
*Qualitative*
**

**Focus group discussions with local stakeholders**

Initial focus group discussions will take place with local stakeholders to further inform the in-depth interviews with infants’ mothers. Four focus group discussions will take place with:

a. Members of the National Nutrition Agencyb. MRCG@LSHTM field workers working on the studyc. MRCG@LSHTM field workers not working on the studyd. Mothers from surrounding villages whose infants are not enrolled in the study

These focus group discussions will last on average one hour and will be conducted in English or Mandinka (the predominant local language) by an investigator and a female local team member trained in qualitative research. The location will be chosen to add comfort and will most likely include the offices of National Nutrition Agency, the facilities of MRCG@LSHTM, local health clinics, and within local villages. Both MRCG@LSHTM staff from the main study and those not working for the pilot study will be interviewed to ensure a wide range of opinions are sought given that staff hiring at MRCG@LSHTM is done by application and staff applying to work on the main study may have different pre-conceived perceptions of the acceptability and necessity of iron supplementation.

**In-depth interviews with infants’ mothers**

The in-depth interviews will discuss the acceptability of iron supplementation in infancy from the perspective of mothers, but data obtained from the focus group discussions will be used to finalize the interview schedules. Using these interview schedules, 30–60-minute individual in-depth interviews will be conducted with mothers whose infants are enrolled in the trial. Interviews will be conducted, in Mandinka, by a qualitatively trained, female member of the study team, and will be audio recorded. In-depth interviews will employ concurrent and retrospective data collection by interviewing mothers during the last four weeks of the trial and in the two-week follow-up window. The location will be chosen by the interviewee to add comfort and will most likely include the homes of participants and within local villages. Data will be collected towards the end of the infant’s enrolment so that mothers have had mostly the full experience until that point.

All answers obtained and information given through both focus group discussions and in-depth interviews will be anonymised, collated, and analysed. NVivo (2020 release) software will be used to analyse qualitative data. 

### Data quality and standards

As per MRCG@LSHTM guidelines, principles of good clinical practice will be adhered to, and all training will be documented. The studies are monitored by the MRCG@LSHTM Clinical Trial Unit. To ensure standardisation of processes, MRCG@LSHTM standard operating procedures with respect to trial management, quality assurance, data management, IT security and statistics will be followed.

### Sample size

We intend to enrol 100 infants in the trial, which will be sufficient to have 80% probability that, if the true increase in geometric mean serum iron concentration in the iron group increases by 70% or more relative to the control group, the 95% confidence interval for the ratio would exclude zero (with the additional assumptions that the variance of log
_e_ serum iron concentration [in µmol/L] is 0.76 for each group
^
13
^; 10% of infants in the iron group stop taking iron supplements in the course of the intervention period; and the percentage of infants in the control group who stop taking placebo supplements is negligible) (
Figure 3). In absolute terms, an increase by 70% corresponds to a change of geometric mean serum iron concentration of 3.0µmol/L, assuming that this concentration is 4.3µmol/L in the placebo group (as observed at Day 0 in Armitage
*et al.* 2019
^
1
^), so that it will have increased 7.3µmol/L in the iron group. We consider intervention effects below 3.0 µmol/L (absolute group difference in geometric means) to be unimportant from medical and public health points of view.

**Figure 3. f3:**
[figure not shown]
Sample size requirements for various intervention effect sizes.

With regards to the mixed methods study, we aim to recruit roughly five participants to each focus group discussion, in accordance with general recommendations for focus group size in qualitative research (20 participants total)
^
14
^. Maximum variation purposive sampling of the mothers whose infants are enrolled in the main study will be used to ensure a wide variety of the dimensions of interest, aiming to identify central themes across this diverse sampler
^
15–
17
^. This will take into consideration various regions, religions, families, ages, and schooling levels. However, all mothers must be Mandinka (the most common local tribe in anticipation that the majority of participants recruited into the main trial will be Mandinka) to provide homogeneity in the translation of the in-depth interviews. An equal number of mothers from the intervention and control arms of the trial will be included, to ensure both perspectives are considered. We anticipate an approximate sample size of 10–20 infants’ mothers.

### Statistical analysis

**
*Main study.*
** Statistical analyses will be performed using R studio and STATA software. Intervention groups will be described using conventional summary statistics (e.g., means or counts with standard deviations, medians with 25- and 75-centiles). The primary analysis concerns the effect of intervention on serum iron concentration at Day 99 (i.e., 98 days of intervention with a 1-day wash-out period after administration of the last supplement, assuming that a transient increase in serum iron concentration following iron supplementation will disappear within this period), adjusted for serum iron concentration measured at baseline. Continuous outcomes will be analysed by linear regression, with transformation of the outcome as needed to normalise the distribution of residuals. Analysis will be by modified intention-to-treat, i.e., all infants who were randomised and who received at least one supplemental dose will be included. We also plan to perform per protocol analysis (i.e., to assess the efficacy that can be attained under controlled conditions) to determine the sensitivity of our modified intention-to-treat analysis. To account for missing data, we will use multiple imputations. In secondary analyses, we will adjust for any group imbalances that may occur in prognostic variables measured at baseline. Serum iron concentrations are known to undergo diurnal fluctuation and they are known to be reduced in inflammation
^
18
^. Thus, to account for these effects, we will also conduct secondary analyses with adjustment for the time of blood collection and for plasma concentrations of C-reactive protein and alpha-1 acid glycoprotein at the time of blood collection.

Group differences in adverse events will be analysed using negative binomial regression. In this analysis, we will count adverse events as the number of days with adverse events divided by the total number of days that the infant was observed during the intervention period. In the analysis of diarrhoea, we will count an event if the parent/guardian reported three or more fluid stools (as indicated by a WHO stool chart) in the previous 24-hour recall period
^
19
^. To produce conservative effect estimates, analyses of adverse events will be per protocol.

Lastly, we will explore to what extent the magnitude of the intervention effect on serum iron concentration depends on iron status at baseline, as indicated by plasma concentrations of ferritin and soluble transferrin receptor (with adjustment for plasma concentrations of c-reactive protein/alpha-1 acid glycoprotein at baseline as inflammation markers).

**
*Mixed methods study.*
** The focus group discussions and in-depth interviews will be recorded and later transcribed and translated (where needed) into English. Translation will occur at MRCG@LSHTM by a trained employee literate in both Mandinka and English.

Data will be analysed with respect to the implementation framework known as
*Acceptability of healthcare interventions: an overview of reviews and development of a theoretical framework* (
Figure 4)
^
20
^.

The qualitative data will be uploaded into, managed, and analysed in NVivo (2020 release) using a Template Analysis Method
^
21,
22
^. The template will be based on the six themes in the acceptability framework, with some minor variation to make analytical sense with regards to our data. By this we mean the framework itself is a macro-level conceptual framework and will require semantic changes to some terminology for it to be useful to analyse at the meso-level (i.e., data from focus group discussions with stakeholders) and at the micro-level (i.e., data from in-depth interviews with women enrolled in the trial). Template analysis follows a methodical six-stage process: 1) Data re-familiarization; 2) Preliminary coding; 3) Thematic organization within the template; 4) Defining the template; 5) Application of template to the full dataset; and 6) Finalization of template definitions. By utilising the acceptability framework as the basis for the analytical template in both the focus group discussions and in-depth interviews datasets-, the qualitative data will be able to be linked coherently across all levels. An analysis in this detail should provide valuable insight about the acceptability of the intervention. We acknowledge that the domains may not all reach saturation, but as these are based on an extensive search of the literature by the framework authors, and have been tested in different fields, we propose to use these as a basis for our analysis. We will later analyse the extent to which the framework was valuable in this evaluation study. 

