## Abstract

**Background:** A recent analysis showed that plasma iron concentrations decline rapidly from birth in Gambian infants, irrespective of sex or birthweight, to concentrations well below normal expected values for iron-replete children older than two months of age (typically >10 μmol/L). The development and function of neural and immune cells may thus be compromised before the minimum age at which children should receive iron supplementation as per World Health Organisation recommendations.

**Methods:** This study is a two-arm, double-blind, placebo-controlled, randomised superiority trial. Infants will be randomised to receive iron drops (7.5mg/day of iron as ferrous sulphate) or placebo daily for 98 days, to test the impact on serum iron concentrations in healthy, breastfed infants (n = 100) aged 6-10 weeks at enrolment. Participants will be visited daily and supplemented by the field team. Daily health and weekly breastfeeding questionnaires will be administered. Anthropometry, and venous blood and faecal samples will be collected at enrolment and after 98 days of supplementation with serum iron as the primary endpoint. Low birthweight (less than 2.5kg at birth) and infants born prematurely (< 37 weeks) will not be excluded. Formula-fed and infants with any illness will be excluded. An additional study exploring maternal stakeholder perspectives of the intervention will be conducted by means of maternal interviews and four focus group discussions with local stakeholders.

**Discussion:** Most breast-fed Gambian infants have very low circulating iron levels by five months of age. This study will introduce iron supplements much earlier in infancy than has previously been attempted in a low-income setting with the primary aim of increasing serum iron concentration.

**Trial registration:** Clincaltrials.gov (
NCT04751994); 12
^th^ February 2021

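### For continuous outcomes other than serum iron, the only stated baseline adjustment is secondary and triggered by imbalance, which forgoes precision a prespecified own-baseline term would give

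*Protocol article*

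**What the plan says.** All of the analysis text comes from the Statistical analysis section (Main study) of the protocol article.

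- **Primary outcome.** Serum iron at Day 99 is compared between arms with adjustment for baseline serum iron.
- **Continuous outcomes in general.** "Continuous outcomes will be analysed by linear regression, with transformation of the outcome as needed to normalise the distribution of residuals". The sentence fixes the model family and the transformation. It lists no covariates, and it does not say that the comparison is unadjusted.
- **Other use of baseline values.** Secondary analyses will adjust for prognostic baseline variables on which the arms happen to differ. This provision is not restricted to serum iron. No threshold for a difference is given.

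The Outcomes section lists the secondary continuous endpoints. The iron-status ones, all defined at Day 99, include haemoglobin, hepcidin, reticulocyte number, erythropoietin and erythroferrone. The growth endpoint is "Anthropometric Z-scores relative to the World Health Organization (WHO) Growth Reference".

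On data collection the Abstract says: "Anthropometry, and venous blood and faecal samples will be collected at enrolment and after 98 days of supplementation with serum iron as the primary endpoint". The Baseline section has height, weight and a full blood count with reticulocytes taken at enrolment, and the Follow up section repeats the blood and anthropometry procedures at the final visit. Under Laboratory evaluations, hepcidin, erythroferrone and erythropoietin are to be measured by ELISA on a serum aliquot, but the text does not say whether the baseline aliquot is assayed.

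**The concern.** The article treats two kinds of continuous outcome differently. Serum iron has a prespecified own-baseline term. Haemoglobin, reticulocytes and the Z-scores have only an adjustment that is secondary and depends on an imbalance being seen in the data.

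That second policy is the weaker one for two reasons. Whether an imbalance has occurred is judged after the data are seen, without a stated criterion. And a trigger based on imbalance misses the main benefit of a baseline covariate, which is to remove explained variation from the residual whether or not the arms differ at baseline.

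What is at stake is the width of the intervals for secondary endpoints. Growth is a named secondary objective and haemoglobin is the first-listed iron-status secondary endpoint. The article presents the trial as groundwork for a larger one, so the precision of these estimates has some use beyond this trial.

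**Working it through.** **1. The plan's own figure.** The Sample size section says: "We intend to enrol 100 infants in the trial, which will be sufficient to have 80% probability". Its inputs are a ratio of geometric means of 1.70 ("geometric mean serum iron concentration in the iron group increases by 70% or more relative to the control group"), a variance of log serum iron that "is 0.76 for each group", a two-sided 5% level, and the assumption that "10% of infants in the iron group stop taking iron supplements in the course of the intervention period".

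- SD on the log scale = √0.76 = 0.872.
- Ratio diluted by non-adherence = 0.9 × 1.70 + 0.1 × 1.00 = 1.63, and ln 1.63 = 0.489.
- n per arm = 2 × (1.960 + 0.842)² × 0.76 / 0.489² ≈ 50, with power 0.800 at 50 per arm.

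The stated 100 infants and 80% power reproduce. The calculation uses no baseline correlation and concerns serum iron only, so the present point does not touch it. The article states no power or detectable difference for any secondary endpoint.

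**2. Precision with and without an own-baseline term.** With n per arm and outcome SD σ, the standard error of the difference between arms is σ√(2/n) without a baseline term and σ√(2/n) × √(1 − ρ²) with one. Here ρ is the within-arm correlation between the baseline and Day 99 values. The loss of one residual degree of freedom out of 98 is ignored.

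Inputs: n = 50 per arm (100 infants, 1:1), so √(2/50) = 0.20. The article gives no ρ, so a range is assumed. The detectable difference at 80% power is (1.960 + 0.842) × 0.20 × √(1 − ρ²), in SD units.

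| ρ (assumed) | SE factor √(1 − ρ²) | Fall in SE | Unadjusted N of equal precision, 100/(1 − ρ²) | Detectable difference (SD) |
|---|---|---|---|---|
| 0 | 1.00 | none | 100 | 0.56 |
| 0.2 | 0.98 | 2% | 104 | 0.55 |
| 0.3 | 0.95 | 5% | 110 | 0.535 |
| 0.5 | 0.87 | 13% | 133 | 0.485 |
| 0.7 | 0.71 | 29% | 196 | 0.40 |

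**3. The same in power and interval width.** Take a true difference of 0.5 SD, chosen only for illustration, tested by a two-sided 5% t test with 50 per arm and standardised effect 0.5/√(1 − ρ²). Power is 69.7% without adjustment, 71.4% at ρ = 0.2, 73.7% at 0.3, 81.6% at 0.5 and 93.4% at 0.7.

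For a Z-score with an assumed SD of 1.0, the 95% interval half-width is 1.984 × 0.20 × √(1 − ρ²). That is 0.40 unadjusted, 0.34 at ρ = 0.5 and 0.28 at ρ = 0.7.

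**4. Chance baseline differences.** The baseline difference between arms has standard error 0.20 SD. A difference above 0.3 SD in either direction corresponds to |z| > 0.3/0.20 = 1.5, which has probability 0.134. At ρ = 0.7 such a difference would shift an unadjusted endline contrast by about 0.7 × 0.3 = 0.21 SD. This is one component of the ordinary sampling error already reflected in the unadjusted standard error. It is not an additional bias.

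**5. Which outcomes have the data.** Haemoglobin, reticulocytes and the Z-scores have values at both visits according to the Baseline and Follow up sections. For hepcidin, erythropoietin and erythroferrone, baseline serum is stored but a baseline assay is not stated.

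**The case against.** A reader might infer that haemoglobin, hepcidin and growth will be analysed unadjusted, with chance baseline differences left in the reported result. The document does not support that reading.

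- The general sentence names no covariates at all. Serum iron is itself a continuous outcome covered by that sentence, yet it is adjusted for baseline. The absence of a covariate there cannot be read as a decision against one.
- Covariates for individual secondary endpoints are commonly left to the analysis plan, which is not shown.
- The planned adjustment for observed imbalances could pick up a difference in baseline haemoglobin or body size.
- Randomisation keeps even an unadjusted comparison unbiased, with valid coverage.
- The size of any gain depends on a correlation that the article does not give. The Introduction describes a rapid fall in haemoglobin after birth, steepest in the fastest-growing infants, so a high correlation for haemoglobin over 98 days cannot be taken for granted. At ρ = 0.2 or 0.3 the gain is small.
- A baseline measurement is not stated for three of the hormone and marker endpoints.

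All of this stands, and it limits the point to precision. It does not remove the point, because the article is not wholly silent. It does state a policy for baseline adjustment beyond the primary outcome, and that policy is conditional and secondary. For outcomes measured at both visits, a prespecified own-baseline term is better, and the article already uses one for serum iron.

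**Conclusion.** The point holds as a minor improvement to secondary endpoints. For haemoglobin, reticulocytes and the anthropometric Z-scores, the only baseline adjustment the article states is triggered by observed imbalance and confined to secondary analyses. This forgoes precision that data already collected would supply.

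The size rests on an assumed correlation: negligible at 0.2, modest at 0.3, and material at 0.5 and above, where the standard error falls by 13% or more. It also rests on 50 analysable infants per arm and a linear relation between the baseline and Day 99 values. There is no bias and no inflation of type I error, and neither the primary analysis nor the sample size is affected. If the analysis plan already includes these terms, a reference to it settles the matter.

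**What to change.** In the Statistical analysis section, and in the analysis plan if it does not already say so, state that each continuous outcome measured at both visits has as its main analysis a linear regression of the Day 99 value on trial arm and the baseline value of the same variable, with both on the transformed scale where a transformation is used.

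Apply this to haemoglobin, reticulocytes and each anthropometric Z-score. Apply it to hepcidin, erythropoietin and erythroferrone only where a baseline assay is done, and say whether it is. The adjustment for observed imbalances can remain as a further secondary analysis.

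The cost is one sentence and one degree of freedom per model. No new data are needed for haemoglobin, reticulocytes or the Z-scores. The Study status section reports recruitment complete, so the statement should be dated before the treatment codes are opened for analysis.
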